#### Bivariate analysis

We will provide the differences (95% CI) in the balance test assessments between baseline and end of intervention, and 6 months and 12 months post-intervention. These measures will be compared between groups by ANOVA or the Kruskall-Wallis test if normality is not assumed.

The Chi-squared test or Fisher’s exact test, depending on the conditions, will be used to analyse the number of falls occurring from 12 months prior to inclusion and 12 months post-intervention.

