Vestibular rehabilitation has proven to be useful in improving the balance of elderly patients with instability [10–12]. Several protocols for vestibular rehabilitation exist (home exercises, Tai-Chi [13], optokinetic stimulus, rotating chairs, dynamic posturography exercises, etc.). Dynamic computerized posturography has proven to be especially useful for elderly patients, because it not only improves the stabilisation of the centre of gravity (where sensorial stimuli are absent or altered), but also improves the stability levels of the patient (and thus reduces the risk of falling) [14, 15]. Its major handicap is probably its cost, which has prevented its dissemination and generalisation.

Two possible solutions are presented here, which may serve to reduce this cost. One of these is optimising and reducing the number of vestibular rehabilitation sessions. This strategy has already proven useful for patients whose lack of balance is caused by reasons other than age [16]. The other option is using cheaper posturography systems; for example, Vertiguard® (Vesticure GmbH, Germany), which allows for the analysis of the motion of the centre of gravity in the course of daily activities, in both static and walking patients, as well as vibrotactile stimulation feedback-assisted rehabilitation [17]. This system has proven to be effective with different pathologies [18, 19], but no extensive and systematic studies have yet been undertaken that compare it with dynamic posturography in the treatment of age-related balance deficits.

For this reason, we suggest that it would be fruitful to undertake a study of vestibular rehabilitation in unstable aged patients, which will permit a double assessment. This study will:Evaluate the optimum number of sessions necessary for a substantial improvement (five vs ten);Compare computerised dynamic posturography (visual feedback) and mobile posturography (vibrotactile feedback).

This study was funded by the project PI1500329, integrated into the Spanish State Plan for R + D + I and funded by the ISCIII-Subdirección general de Evaluación y Fomento de la Investigación and the Fondo Europeo de Desarrollo regional (FEDER).

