## Methods and design

### Aim of the study

The primary objective is to evaluate the effectiveness of a mobile posturographic system with vibrotactile neurofeedback to improve balance in elderly patients. Each subject was assessed immediately after the rehabilitation.

The secondary objectives are:To verify that improvements in balance are maintained in the medium term (six to twelve months).To consider whether this improvement in balance results in a reduction in the number of falls suffered by the elderly.To assess whether the reduction in the number of vestibular rehabilitation sessions (five) leads to similar results (an improvement in balance and a reduction in the number of falls) to those obtained after ten sessions. Both rehabilitation systems are compared using computerised dynamic posturography and mobile posturographic with vibrotactile neurofeedback.

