### Design

This study is the continuation of a previous clinical trial conducted by our research group [14], comparing three different rehabilitation strategies (dynamic posturography exercises, optokinetic stimuli and exercises at home) and a control group, to improve balance in elderly. The design of both studies is similar.

This is a randomized controlled trial. It is an experimental study, single-centre, open-label and randomized (balanced blocks of patients) in four parallel branches. It involves 220 elderly patients (over 65 years of age) who are at high risk of falling, and a 12-month follow-up period will be applied.

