### Randomisation and intervention

#### Visit 1

After the first screening visit, the patients who provided consent will be included in the study and randomised to one of the following study arms:A.**Intervention with dynamic computerized posturography exercises (ten sessions)**. The Smart Equitest program was used: 10 exercises per session, which were customized depending on each patient’s deficit (as observed in the earlier postural study), were undertaken. The exercises involve visual biofeedback together with sensitive, real-time monitoring of movement. For some exercises, patients must maintain their centre of gravity (COG) over the base of support, while for others the COG must be moved to a series of targets. In addition, the support surface and/or visual surround may also move in response to the patient’s own movement. The exercise difficulty was progressively increased throughout the rehabilitation sessions by increasing the LOS, the transition rate or the movement of the posturography platform. The duration of each session was approximately 15 min. The distribution of sessions was one per day and five per week (two weeks)B.**Intervention with dynamic computerized posturography exercises (five sessions)**. Same as Group A, except for the number of sessions (5) and their distribution (one session on alternate days, for two weeks).C.**Intervention with mobile posturography (Vertiguard) exercises (ten sessions)**. As many as six tasks were set, and the most prominent deviations from normative control values were included in the training programme. Individual feedback was stored in the device for each patient based on body sway analysis. Training was performed using the training function of Vertiguard-RT device. This neurofeedback system contains a battery-driven main unit which is fixed on a belt at the centre of the body mass (hip) and one vibration stimulator on the front, back, left and right side, respectively. Vibration stimulators are mounted on the same belt as the main unit. They were adjusted by sliding them over the belt to the correct position for the individual patient. The main unit continuously determines the Coriolis force during body movements (pitch and roll) using inbuilt gyroscopes and compares those values with individual pre-set thresholds for stimulator activation in specific directions.Training was performed daily under the supervision of a physician over 2 weeks (over 10 sessions and the weekend was excluded). A training session consisted of 5 repetitions of six selected training tasks as described above (each repetition lasted 20 s or until the movement was finished). The patient received a vibrotactile feedback signal during training for those directions when a body sway higher than pre-set thresholds was noted. Vibration was reinforced with increasing sway: the more it exceeded the pre-set values, the stronger the vibration was at the corresponding site.No vibrotactile feedback was applied if the patient’s sway was below pre-set thresholds. The exercise difficulty progressively increased throughout the rehabilitation sessions by pressing the sensitivity buttons (up/down) on the main unit. During this procedure, the individual pre-set thresholds were similarly decreased for all sway directions of the specific training conditions until the patient perceived a vibration while performing the training task.D.**Intervention with mobile device Vertiguard exercises (five sessions)**. Same as Group C, except for the number of sessions (5) and their distribution (one session on alternate days, for two weeks).

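### The four arms cross device with session number, but neither stated analysis is set up to estimate the effect of either factor

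*Protocol article*

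**What the plan says.** The protocol article, Background, sets two tasks: "Evaluate the optimum number of sessions necessary for a substantial improvement (five vs ten") and "Compare computerised dynamic posturography (visual feedback) and mobile posturography (vibrotactile feedback"). The Design section describes the trial as "randomized (balanced blocks of patients) in four parallel branches".

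Under Randomisation and intervention, arm A is ten sessions of dynamic posturography and arm C is ten sessions on the mobile device. Arm B is "Same as Group A, except for the number of sessions (5") and their spacing. Arm D is "Same as Group C, except for the number of sessions (5") and their spacing.

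The Aim of the study section makes the effectiveness of the mobile system the primary objective. Among the secondary objectives it asks whether five sessions "leads to similar results (an improvement in balance and a reduction in the number of falls) to those obtained after ten sessions".

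Two analyses of balance are stated:

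- **Bivariate analysis.** Changes from baseline to end of intervention, 6 months and 12 months are given with 95% CIs. Then: "These measures will be compared between groups by ANOVA or the Kruskall-Wallis test if normality is not assumed".
- **Multivariate analysis.** A mixed or GEE model of visits 2, 3 and 4 takes account of the covariables. Treatment is one fixed factor, and SOT balance at baseline and over follow-up is called a random effect.

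The article names no device term, session term, interaction or planned contrast.

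**The concern.** A test of whether any of four arms differs does not say which factor is responsible. If it is significant, the reader cannot tell whether device or session number made the difference. If it is not, the result may be taken to mean that five sessions do as well as ten, which a non-significant test cannot show.

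The CIs promised in the Bivariate analysis section do not fill the gap, because they describe change from baseline and not a contrast between devices or session numbers.

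The overall test also spends three degrees of freedom where each question needs one. Following it with comparisons of single pairs of arms would use only half of the patients for each question.

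**Working it through.** **1. The crossing.**

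| | Ten sessions | Five sessions |
|---|---|---|
| Dynamic posturography | A | B |
| Mobile posturography | C | D |

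Device is (A, B) against (C, D), and session number is (A, C) against (B, D). With 55 per arm, each comparison is 110 against 110. The session factor includes the spacing, since both schedules run over two weeks.

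**2. The plan's own figure.** Calculation of sample size gives 95% confidence, power 0.80, a 10-point change and 53 per arm. The totals are right: 4 x 53 = 212 and 4 x 55 = 220. The 53 itself cannot be reproduced, because no SD is stated. A two-sided two-sample comparison with 53 per arm detects

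(1.960 + 0.842) x sqrt(2/53) = 0.544 SD.

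For 10 points this implies SD = 10/0.544 = 18.4 (18.2 by the t distribution); for 9 points it implies 16.5. Other readings (one-sided testing, or Bonferroni over six pairs) give about 13 to 21. A paired before-after formula gives an SD of change of 23 to 26. The 10 points are a before-after change, so 18.2 is only a working value.

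**3. Assumptions for the illustration.** SD 18.2; 53 per arm; a 5-point effect of one factor; no effect of the other and no interaction; baseline-outcome correlation r between 0.5 and 0.8; two-sided 0.05.

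**4. Formulas.**

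- SD of change = 18.2 x sqrt(2(1 - r)): 16.3 at r = 0.6, 14.1 at r = 0.7.
- Baseline-adjusted SD = 18.2 x sqrt(1 - r^2): 14.6 at r = 0.6, 13.0 at r = 0.7.
- Noncentrality with one active factor = N x (effect/SD)^2 / 4. On change at r = 0.6: 212 x (5/16.28)^2 / 4 = 5.0. The value is the same for the overall test (3 df) and the main effect (1 df), so the loss comes from the degrees of freedom alone.

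**5. Power.**

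| r | One pair of arms, change | Four-group test, change | Main effect, change | Main effect, baseline-adjusted |
|---|---|---|---|---|
| 0.5 | 29% | 35% | 51% | 63% |
| 0.6 | 35% | 43% | 60% | 70% |
| 0.7 | 44% | 56% | 73% | 80% |
| 0.8 | 60% | 75% | 88% | 91% |

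At r = 0.6 the approximate 95% CI half-width is 1.96 x 16.28 x sqrt(2/53) = 6.2 points for one pair on change. For the baseline-adjusted main effect it is 1.96 x 14.56 x sqrt(2/106) = 3.9 points.

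**6. The same comparison without an SD.** With the effect in SD units of the analysed score and N = 212, the overall test has 42% power against 59% for the main effect at 0.30 SD, 64% against 80% at 0.385 SD, and 92% against 98% at 0.544 SD. For 80% power at 0.385 SD, the overall test needs 300 patients and the main effect 216.

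**7. Where the picture changes.**

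- With a 10-point effect of one factor, the overall test on change has 97% (r = 0.6) to 99.5% (r = 0.7) power, against 99% to 99.9% for the main effect. The loss nearly vanishes.
- With both factors at 5 points, the overall test rejects 75% (r = 0.6) to 87% (r = 0.7) of the time. That is more often than a single main effect, but it attributes the result to neither factor.

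**The case against.** **Baseline adjustment.** The bivariate comparison is not the whole plan. The Multivariate analysis section holds the model meant to assess efficacy, and it brings in baseline SOT and the covariables. A reader might infer that the plan ignores the baseline measurement, but the documents do not support that. What stands is that calling baseline SOT part of a random effect leaves its role unclear. The baseline-adjusted column above therefore shows the gain over the bivariate step only, not over that model.

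**Whether the factors can be recovered.** Both factor effects are linear contrasts of a four-level treatment factor, with the same precision as in a 2x2 model with interaction. An analysis plan not shown could name them. It would therefore be too strong to say that the design or the planned model cannot answer the two questions. The four-group reading of the ANOVA is also an inference, although Kruskal-Wallis as its direct substitute makes it the natural one. What stands is that the article fixes a between-group test that does not match its own questions.

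**Size.** The power figures rest on an SD solved backwards from a before-after change, a 5-point effect that the documents do not support, an assumed correlation and one active factor. They are illustrative and do not show that the trial is underpowered.

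**The rank test.** A rank-based fallback is conventional. It gives no factor effect on the SOT scale, however, so it should not be the main comparison.

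**Conclusion.** The point holds in limited form. The arms are a 2x2 design, and as written neither analysis yields a direct estimate with confidence interval for device or for session number. Under the stated assumptions, moving from the four-group test on change to a baseline-adjusted main effect raises power from 43% to 70% at r = 0.6 and from 56% to 80% at r = 0.7. The case does not depend on those figures: in every scenario the overall test leaves the effect unattributed.

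A reader might infer that a 2x2 model by itself settles five versus ten sessions. It does not. The Aim of the study section asks whether results are similar, and that needs a confidence interval judged against a margin; the article states none. Main effects also average over the other factor and can mislead if the interaction is strong.

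**What to change.** Make the between-group SOT analysis a baseline-adjusted model with fixed terms for device, session number and their interaction. This can be an ANCOVA of visit 2 SOT, or the planned repeated-measures model with baseline SOT as a fixed covariate, which also covers 6 and 12 months.

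- Report each main effect (about 110 against 110) with its 95% CI.
- Report the interaction with its CI, and the four arm means. The interaction, taken as a difference of differences, has twice the standard error of a main effect (sqrt(4/53) against sqrt(2/106), times the SD), so a non-significant interaction must not be read as absence of one.
- State a margin for five versus ten sessions before the data are analysed, and judge similarity from the CI against it.
- Keep Kruskal-Wallis at most as a sensitivity analysis.

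The cost is a change of wording, a little analysis work and agreement on a margin. No further patients or measurements are needed.

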## Background

Accidental falls, especially for the elderly, are a major health problem in Western society [1, 2]. Approximately one-third of those over 65 suffer at least one fall per year; among those over the age of 85, this rises to approximately half. Furthermore, those who fall will often fall regularly (several times per year).

The repercussions of these falls in terms of morbimortality are serious, particularly because of associated bone fractures. Especially grave are hip fractures. Even if bone fractures do not result from the fall, the psychological consequences of falls seriously affect the quality of life of those affected. People who have suffered a fall tend to fear that this will happen again, and thus to reduce their physical activity. This, in turn, increases the chances of new falls and increases levels of fear, in a vicious circle that often leads to isolation and increasing dependency on carers [3].

In addition to these clinical and psychological consequences, the economic repercussions of the problem are also serious. The direct healthcare expenditure of these falls is very high, and the indirect cost of the recovery process and the monitoring thereafter is also very significant; there is the cost of increased care, and of adapting the home to the person’s new needs (ramps for wheelchairs, lifts and/or elevating platforms, handles in bathrooms) as well as the expense of other mobility equipment (walking supports, crutches, walking frames, etc.).

Many factors contribute to the risk of falls [4], including problems in the central nervous system that affect coordination and motion, balance disorders of different origins (vestibular, locomotor, visual, etc.), and advanced age [5] and age-related sensorial impairments [6, 7]. Several strategies can minimise risk [8, 9]; it is important to identify those in gravest danger of falling, in order to implement the necessary precautionary measures and to prevent (or at least to slow down) the age-related causes of falls using training and rehabilitation.

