### Inclusion criteria

Persons at a high risk of falling shall meet at least two of the following requirements:They have fallen at least once over the last 12 months.They required more than 15 s to complete, or require support in, the TUG test.They obtained a mean CDP SOT balance score of < 68%.They have fallen at least once in the CDP SOT.They obtained a score in Vertiguard’s gSBDT of > 60%.

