### Variables

The study variables shall be as follows:Date of birth.Sex.Weight (kg) and height (cm).Number of falls in the 12 months before inclusion.Hospitalisations due to falls over the previous 12 months.Percentage of mean balance (average) as observed in computerized dynamic posturography (CDP) sensory organisation test (SOT) (PRIMARY ENDPOINT); this will be obtained by calculating the mean of the scores of the 18 records of each sensory organisation test (calculated by software).DHI score: covered by patient.Short FES-I score: covered by patient.Duration (seconds) of TUG: measured by evaluator.Number of steps in TUG: measured by evaluator.Number of supports in TUG: measured by evaluator.Mean value of CDP SOT condition 5: calculated by software.Mean value of CDP SOT condition 6: calculated by software.CDP SOT vestibular contribution value: (mean value of condition 5/mean value of condition 1) × 100.Mean value of directional control of limits of stability in CDP: calculated by software.Mean endpoint value and maximum travel point of limits of stability in CDP: calculated by software.Vertiguard gSBDT value: calculated by software.Number of falls over 12 months after completion of VR programme (we will give the patient a timetable to allow them to check each fall immediately after it happens, in order to avoid memory bias).Hospitalisation resulting from those falls: date, diagnosis, duration of hospitalisation.

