### Analytical plan and statistical measures

The patients’ demographic data and characteristics will be described globally and by the covariables of interest, as will the patients’ results.

The continuous results will be summarised as mean, median, standard deviation (D) and interquartile range (P25, P75). For the categorical results, we will present the number and percentage of patients in each category.

The statistical analyses will be based on the complete analysis group (CAG), which comprises all the subjects (those who granted informed consent and met all the inclusion and exclusion criteria, and were randomised to one of the study arms).

**The outcomes** of interest are: balance assessment (average balance score in CDP SOT and Vertiguard’s gSBDT score, with possible values 0–100 in both); assessment of instability perception scales (DHI, short FES-I) on visits 2 (after intervention), 3 (6 months after intervention) and 4 (12 months after intervention); number of falls at 12 months post-intervention.

**The covariables of interest** are:Baseline patient characteristics: they include the variables specified for visit 0.Associated risk factors: age, sex, weight (kg), height (cm), previous falls (yes/no).Adherence to intervention (investigator’s direct observation).

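### The only falls analysis named is a chi-squared or Fisher test across the years before and after training, which on its natural reading cannot show whether training reduced falls

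*Protocol article*

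**What the plan says.** All places are in the protocol article.

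- **Bivariate analysis.** The method for falls is "The Chi-squared test or Fisher’s exact test, depending on the conditions", which "will be used to analyse the number of falls occurring from 12 months prior to inclusion and 12 months post-intervention". No other falls analysis is given. The model under Multivariate analysis is Gaussian and concerns the SOT balance score.
- **Aim of the study.** A secondary objective is "To consider whether this improvement in balance results in a reduction in the number of falls suffered by the elderly".
- **Analytical plan and statistical measures.** The outcome is "number of falls at 12 months post-intervention", a count per patient. The Abstract calls it a rate, and the Background notes that people who fall often do so several times a year.
- **Inclusion criteria.** "Persons at a high risk of falling shall meet at least two of the following requirements". One of the five is "They have fallen at least once over the last 12 months", so a prior fall helps a patient qualify but is not required.
- **Variables, and the limitations in the Discussion.** For later falls, "we will give the patient a timetable to allow them to check each fall immediately after it happens". Earlier falls are recalled. The authors acknowledge memory bias and plan to check with a relative and the medical record.
- **Randomisation and intervention.** All four arms receive training (two devices, ten or five sessions). None is untreated.

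**The concern.** Chi-squared and Fisher tests need independent observations in categories. Here each patient contributes to both periods, and the outcome is a count of repeated events.

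The design adds a more serious problem. The earlier year is partly selected on the variable under test, because a fall in that year counts towards entry. The two years are also ascertained differently. With no untreated arm, nothing separates a training effect from regression to the mean or from the change in recording. A p-value from this comparison could be reported as the answer to the falls objective, in either direction, with no treatment effect behind it. Meanwhile the contrast that randomisation protects, falls after training between arms, has no clear analysis.

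**Working it through.** The protocol gives no numerical figure for the falls analysis, so there is none to reproduce. Its 53 per arm is for the SOT score and has no bearing here. The check is how the planned test behaves when training does nothing.

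**Inputs from the protocol.** N = 220. Background risk of at least one fall a year: one third ("Approximately one-third of those over 65 suffer at least one fall per year"), or about one half over age 85. Entry by at least two of five criteria.

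**Assumptions, not in the documents.** Each patient has one fall rate for both years, drawn from a gamma distribution with shape k and mean m; counts are Poisson given that rate. The test compares any fall (yes/no) before and after. The share of prior fallers, k and the completeness of recall are varied.

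**Step 1: later risk given earlier falls.** P(no fall in one year) = (1 + m/k)^(−k). P(no fall in either year) = (1 + 2m/k)^(−k). With k = 1:

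- Risk 1/3: m = 0.5; no fall in either year = 1/2; falls in both = 1 − 2(2/3) + 1/2 = 1/6. Later risk is (1/6)/(1/3) = 0.50 for prior fallers and (2/3 − 1/2)/(2/3) = 0.25 for the others.
- Risk 1/2: m = 1; no fall in either year = 1/3; falls in both = 1 − 1 + 1/3 = 1/3. Later risk is 2/3 for prior fallers and 1/3 for the others.

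**Step 2: cohort with a given share s of prior fallers.** Share falling afterwards = s × (prior-faller risk) + (1 − s) × (other risk).

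| Background risk | s (before) | After | Null rejection, chi-squared |
|---|---|---|---|
| 1/3 | 50% | 37.5% | about 84–86% |
| 1/3 | 40% | 35% | about 11% |
| 1/3 | 33% | 33% | about 0% |
| 1/2 | 60% | 53% | about 19–20% |
| 1/2 | 50% | 50% | about 0% |
| 1/2 | 40% | 47% (increase) | about 20%, by symmetry with the 60% row |

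First row by hand: the pooled proportion is 0.4375, so the standard error is √(2 × 0.4375 × 0.5625/220) = 0.0473. Significance needs a drop of 1.96 × 0.0473 = 0.0927, or 20.4 patients. The expected drop is 0.125 × 220 = 27.5, with SD √(110 × 0.25 + 110 × 0.1875) = 6.94. Φ((27.5 − 20.4)/6.94) = Φ(1.02), about 85%. For that row, k = 0.5 gives about 59% and k = 2 about 94%.

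**Step 3: simulate the entry rule itself.** Suppose each of the other four criteria is met independently with probability q (risk 1/3, k = 1, full recall).

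| q | Any fall before → after | Chi-squared rejects | McNemar rejects |
|---|---|---|---|
| 0.2 | 62% → 41% | 100% | 100% |
| 0.4 | 45% → 37% | 47% | 56% |
| 0.6 | 37% → 34% | 5.5% | 8% |
| 0.8 | 34% → 33% | 2% | 5% |

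Over risks 1/3 and 1/2 and k from 0.5 to 2, chi-squared rejects in 92–100%, 15–60%, 1–8% and 0.5–3% of null trials for these four values of q.

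**Step 4: ignoring the pairing, alone.** With no selection on falls, the unpaired test rejects in 0.5–3.4% of null trials against a nominal 5%; McNemar rejects in 3–4%. Ignoring positive within-patient correlation makes the test conservative.

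**Step 5: recall.** Risk 1/3, k = 1. If 80% of earlier falls are recalled, the change is 40% → 37% at q = 0.4 but 29% → 33% at q = 0.8. If 60% are recalled, it is 33% → 36% and 24% → 34%. Under-recall can cancel or reverse the false reduction.

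**The case against.** **A false reduction is not certain.** A reader might infer that the test will show fewer falls even if training does nothing. The documents do not support that. A prior fall is one of five criteria, any two suffice, and the share of patients entering with one is not given. If that share matches the cohort's underlying risk, the artefact vanishes. A high-risk cohort may well exceed the one-third risk quoted for the general population over 65, and under-recall pushes the other way. This stands.

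**The unpaired test does not cause the artefact.** A reader might blame the choice of chi-squared. Step 4 shows that ignoring the pairing errs towards missing a difference, and Step 3 shows McNemar inflated in the same settings. The cause is selection plus an uncontrolled comparison. This also stands.

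**The sentence may mean something else.** The preceding paragraph compares measures between groups, so a comparison of arms within each period is possible. It is less natural, given the wording and the stated objective. Under it, testing pre-inclusion falls between randomised arms says nothing about treatment, and the later comparison would still reduce a count to categories. The sentence needs rewriting either way.

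**Recall is mitigated.** Checks with a relative and the medical record help, but do not make recalled and diary-recorded falls equivalent.

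**Incomplete follow-up.** That the article does not say how follow-up shorter than 12 months is handled is a detail an analysis plan would commonly settle. It is not counted here.

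**Conclusion.** The concern holds in this form: on its natural before-after reading, the one falls analysis the protocol names cannot answer the falls objective. The test does not suit repeated counts in the same patients. The decisive point is that, with entry partly on prior falls, unlike ascertainment and four active arms, no before-after change can be attributed to training.

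The size and direction of the error are unknown. Under the assumed model, null rejection runs from almost nil to nearly certain, and the apparent change can be a fall or a rise. It depends on the share of prior fallers, the cohort's background risk, between-patient variation and recall, none of which the documents give for these patients. The percentages are illustrations of that range, not predictions.

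This should be fixed. It is not critical to the trial, because falls are secondary and the SOT analysis is untouched.

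**What to change.** Replace the sentence on falls under Bivariate analysis. Compare the number of falls after training between the randomised groups (device, number of sessions) by negative binomial regression, with log follow-up time as offset and the number of prior falls as a covariate, entered as a count. Report rate ratios with 95% confidence intervals. Show before-after numbers descriptively only, and draw no causal conclusion about fall reduction from them. If a between-arm test was always intended, say so and use the same count model.

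The cost is wording and a standard model, since the protocol already collects fall counts for both periods. The downside is that the before-after p-value is given up, and the trial can conclude only on differences in falls between active arms. The falls objective under Aim of the study should be reworded to match.
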